## Abstract

**Background:**

Treatment options for patients with inherited retinal disease are limited, although research into novel therapies is underway. To ensure the success of future clinical trials, appropriate visual function outcome measures that can assess changes resulting from therapeutic interventions are urgently required. Rod-cone degenerations are the most common type of inherited retinal disease. Visual acuity is a standard measure but is typically preserved until late disease stages, frequently making it an unsuitable visual function marker. Alternative measures are required. This study investigates the clinical utility of a range of carefully selected visual function tests and patient reported outcome measures. The aim is to identify suitable outcome measures for future clinical trials that could be considered for regulatory approval.

**Methods:**

This cross-sectional study involves two participant groups, patients with inherited retinal disease (n = 40) and healthy controls (n = 40). The study has been designed to be flexible and run alongside NHS clinics. The study is split into two parts. Part one includes examining standard visual acuity, low luminance visual acuity, the Moorfields acuity chart visual acuity, mesopic microperimetry and three separate patient reported outcome measures. Part two involves 20 min of dark adaptation followed by two-colour scotopic microperimetry. Repeat testing will be undertaken where possible to enable repeatability analyses. A subset of patients with inherited retinal disease will be invited to participate in a semi-structured interview to gain awareness of participants’ thoughts and feelings around the study and different study tests.

**Discussion:**

The study highlights a need for reliable and sensitive validated visual function measures that can be used in future clinical trials. This work will build on work from other studies and be used to inform an outcome measure framework for rod-cone degenerations. The study is in keeping with the United Kingdom Department of Health and Social Care research initiatives and strategies for increasing research opportunities for NHS patients as part of their NHS care.

**Trial registration:**

ISRCTN registry, ISRCTN24016133, Visual Function in Retinal Degeneration, registered on 18th August 2022.

**Supplementary Information:**

The online version contains supplementary material available at 10.1186/s12886-023-02974-6.

## Background

Inherited retinal diseases are the leading cause of blindness in the working age population in the United Kingdom. Retinitis pigmentosa (RP) is the most common inherited retinal disease and typically presents as a rod-cone degeneration [1, 2]. These patients present with reduced night vision and peripheral visual field loss, which progresses centripetally inward and radially outward. The central vision is often spared until late disease stages. Severe visual impairment occurs when the degeneration encroaches on the central retina [2].

There are over 50 genes associated with RP and over 277 genes associated with inherited retinal disease, each with a specific disease mechanism and clinical presentation. These include the age of presentation, disease severity, rate of disease progression and sometimes syndromic manifestations [3, 4].

Currently there is only one approved treatment for a specific and rare early onset retinal dystrophy called *RPE65-*associated retinal dystrophy, this has been approved by United States Food and Drug Administration (FDA) and European Medicines Agency (EMA). There are currently no treatments for any of the other causes of inherited retinal disease, although many clinical trials are underway [2]. To ensure that meaningful outcomes of such clinical trials are captured, appropriate visual function assessments must be selected as outcome measures.

Visual acuity (VA), often referred to as Best Corrected Visual Acuity (BCVA), is the standard measure of visual function, despite it being an insensitive marker of early and subtle visual function changes in many retinal conditions [5, 6]. VA incorporates recognition of high contrast letters in high luminance conditions and only reflects the function of the central 0.5 degrees of vision, mediated by a population of foveal cones. In patients with RP, the fovea is typically preserved in early-to-moderate disease stages, so VA remains unaffected, producing a ‘normal’ result. VA only begins to deteriorate as the patient reaches advanced end-stage disease [5]. Currently, for approval of a new treatment based on VA alone, the FDA require a VA gain of 15 letters [7]. Since many patients with RP have preserved VA, many patients have little scope for further improvement, which limits the potential for regulatory approval when using this measure. These limitations are not unique to rod-cone degenerations but have also been reported for other conditions such as age-related macular degeneration and glaucoma [8, 9].

Alternative visual function measures are available and include full visual field assessments, such as kinetic perimetry. However, these tests are time consuming, tiring for patients, highly variable and in patients with RP who typically have very constricted visual fields, a lot of time is spent assessing areas with no remaining visual function [10]. Visual electrophysiology enables objective assessments of visual function. However, these techniques are complex, they require specially trained personnel, take a long time to perform and testing conditions must be carefully controlled to reduce noise in the data [11]. Full-field electroretinography testing is often insensitive to subtle changes in retinal sensitivity or not measurable in many patients with rod-cone degenerations [12]. Furthermore, full-field electroretinography provides a global retinal function assessment as opposed to a measure of localised functional changes, that is required in assessment of targeted therapeutic treatments.

Many of the standard clinical visual function measures currently employed are insensitive to changes due to novel therapies for these rod-cone degenerations [13]. Without suitable outcome measures, treatment effectiveness cannot be determined, delaying any patient benefit. This problem is not confined to inherited retinal disease but also apparent in other conditions such as age-related macular degeneration. The MACUSTAR consortium was set up to identify useful outcome measures for both clinical trials and clinical practice in age-related macular degeneration [6]. To address this need in severely low vision patients the HOVER consortium was formed [14]. Neither of these consortia addresses the problems in patients with early-to-moderate inherited retinal disease causing rod-cone degeneration.

Patients with rod-cone degenerations report difficulty in low light conditions [2], so visual function tests designed to measure function under low light levels may be more sensitive and could allow for more accurate metrics of disease progression and be more relevant to patient experiences. This study aims to investigate the clinical utility of a range of selected visual function tests and patient-reported outcome measures, to identify those suitable for use as outcome measures in future clinical trials to support regulatory approval.

## Methods

The VFIRD study is a cross-sectional prospective study involving two groups of participants: participants with an inherited retinal disease causing a rod-cone degeneration (n = 40), and age and gender matched healthy controls (n = 40). Healthy controls will be recruited from members of the general public through advertisements or from individuals accompanying patients (must be non-blood relatives) to eye hospital appointments. Patient participants will be recruited from the NHS specialist ocular genetics clinic at Oxford Eye Hospital. This publication refers to protocol version 2.1 dated 22/11/2022 and was developed using the STROBE and SPIRIT reporting guidelines where applicable [15, 16]. The study is sponsored by the University of Oxford. A patient and public involvement (PPI) group was set up with representatives providing feedback which supported the study design. Ethics approval has been obtained from the NHS Health Research Authority Black Country Research Ethics Committee (reference 20/WM/0283).

### Study outcomes

Primary outcome: To assess the utility, validity and reliability of current visual function tests as clinical and research measures, in patients with inherited retinal degeneration.

Secondary outcome: To assess the utility, validity and reliability of new visual function tests as clinical and research markers in patients with inherited retinal degeneration.

To gain understanding of patient participant experiences and feelings about these alternative tests and identify whether they are appropriate, acceptable, and accessible, or whether any changes need to be made.

### Exploratory outcomes

To gain a greater insight into genotype-phenotype correlations for specific causes of rod-cone degeneration.

### Screening

Patient participants will be screened from the NHS genetics clinic (Table 1) and invited to take part in the study a least two weeks in advance of their appointment, where upon interest in the study they will be provided with the participant information sheet. The PPI group advised that two weeks should be the minimum time to ensure participants have time to consider their enrolment and make travel plans. Control participants, upon interest in the study, will be provided with the study information sheet to decide if they fulfil the criteria (Table 1) and consider if they wish to take part.

**Table 1 Tab1:** Summary of the VFIRD study eligibility criteria

Inclusion criteria
**The patient participant may enter the study if ALL the following apply:**
• Participant is willing and able to give informed consent for participation in the study
• An inherited retinal degeneration diagnosis
• A minimum of 6/60 (logMAR 1.0) standard VA in each eye
• Able to participate in visual function testing
**The control participant may enter the study if all the following apply**:
• Participant is willing & able to give informed consent for participation in the study
• Male or female, aged 16 or above, there is no upper age limit
• A minimum standard VA of 6/7.5 (logMAR 0.10) in each eye – this will only become apparent once the participant starts the study, if it is clear they do not meet this criterion, they will be excluded from the study and no further testing undertaken
• Able to participate in visual function testing
**Exclusion criteria**
**The patient may not enter the study if ANY of the following apply**:
• Pre-existing amblyopia or squint would exclude that eye, but the unaffected eye would still be eligible
• History of eye problems, eye treatment or eye surgery other than refractive error. If an eye problem exists in one eye, the fellow eye is still eligible
• Been involved in an interventional research trial where they have received a treatment for their eye condition
**Control participants may not enter the study if ANY of the following apply**:
• Pre-existing amblyopia or squint, fellow eye still eligible
• History of eye problems, eye treatment or eye surgery other than refractive error. If an eye problem exists in one eye, the fellow eye is still eligible

### Study procedures

Informed consent will be obtained, in person, by the investigator (appointed research optometrist) prior to completing any study procedures. This is a single visit study that has been carefully designed to fit in and around the NHS outpatient appointments at Oxford Eye Hospital, to minimise the need for participants to return to the eye hospital to take part in the study on a separate day. This is important as the specialist retinal genetic clinics are part of a tertiary referral centre, meaning that patients travel from all over the country to attend. The study has been planned to be as flexible as possible to work around time and room availability constraints, therefore not all the study tests are required to be completed. The study is divided into two parts, part one and part two (Fig. 1). Participants must complete all tests in a single part, although where possible participants will be invited to complete the entire study. A subset of patient participants will be invited to take part in semi-structured qualitative virtual interviews upon completion of the study. Estimated study duration is one hour for each part, two hours in total for the entire study.

**Fig. 1 Fig1:**
[figure not shown]
Illustrates the visual function tests included in part one and part two of the study alongside the testing order

### Part one

#### Patient reported outcome measure questionnaires

Three visual function and quality of life questionnaires (Visual Function Question-25, the Low Luminance Questionnaire and the EQ-5D-5L) are included in the study. To the best of our knowledge, there is little literature around the use of the Low Luminance Questionnaire and EQ-5D-5L for patients specifically with inherited retinal disease. Patients will be required to complete these, ideally before further visual function testing.

#### Refraction and acuity tests

Refractions will be performed at 4m, in accordance with the Early Treatment Diabetic Retinopathy Study (ETDRS) Chart (Fig. 2A) and protocol [17]. This protocol standardises the assessment of VA in clinical trials and remains a prominent functional assessment in most ophthalmic clinical trials.

**Fig. 2 Fig2:**
[figure not shown]
(**A**) is an example of the standard ETDRS chart. (**B**) illustrates low luminance visual acuity, simulating the view of the ETDRS chart through the 2.0 log unit neutral density filter. (**C**) is the Moorfields Acuity Chart

Low luminance VA (Fig. 2B) will be measured first following refraction, using a 2.0 log unit neutral density filter placed in front of the patient’s right eye, with the room lights switched off and using the retro illuminated standard ETDRS visual acuity chart (luminance 1.6 cd/m^2^). The none testing eye will be occluded throughout. Table 2 details the VA test, eye and corresponding letter chart (R, 1 or 2) testing order. The letter charts are rotated at each assessment to limit any letter sequence memorisation.

**Table 2 Tab2:** Visual acuity, eye and corresponding letter chart testing sequence

Visual acuity testing sequence and letter chart rotation
1. Refraction of both eyes, using chart R
2. Right eye low luminance VA, left eye occluded, chart 1
3. Right eye standard VA, left eye occluded, chart 1
4. Left eye low luminance VA, right eye occluded, chart 2
5. Left eye standard VA, right eye occluded, chart 2
6. Repeat right eye low luminance VA, left eye occluded, chart R
7. Repeat right eye standard VA, left eye occluded, chart R
8. Binocular low luminance VA, chart 1
9. Binocular standard VA, chart 1
10. Left eye MAC VA, right eye occluded chart 2
11. Right eye MAC VA, left eye occluded, chart 1
12. Repeat left eye MAC VA, right eye occluded, chart 2
13. Binocular MAC VA, chart 1

The Moorfields Acuity Chart (MAC) is a modified version of the ETDRS letter chart (Fig. 2C), it has been developed to be a more sensitive measure of early changes in central cone photoreceptor disease in age-related macular degeneration. The chart uses vanishing optotypes, whereby, once the letter is no longer recognisable it is also undetectable [8]. MAC chart assessment follows LLVA and standard VA assessment, with the room lights switched on. Again, table 2 details the eye testing order and corresponding chart to use.

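### Table 2 tests and retests the left eye on the same Moorfields chart (chart 2), so the Moorfields repeatability estimate is likely to be too favourable

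*Protocol article*

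**What the plan says.** Under Refraction and acuity tests, the protocol article states its chart rule and the reason for it: "The letter charts are rotated at each assessment to limit any letter sequence memorisation". It also says "Table 2 details the VA test, eye and corresponding letter chart (R, 1 or 2) testing order", and the last sentence of that section makes Table 2 govern the MAC as well.

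In Table 2 the first MAC measurement of the left eye is "10. Left eye MAC VA, right eye occluded chart 2". A single reading by the other eye, on chart 1, comes next. The left eye is then measured a second time: "12. Repeat left eye MAC VA, right eye occluded, chart 2".

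For low luminance VA, the right-eye test and retest are "2. Right eye low luminance VA, left eye occluded, chart 1" and "6. Repeat right eye low luminance VA, left eye occluded, chart R". Standard VA follows the same pattern in rows 3 and 7. The sequence opens with "1. Refraction of both eyes, using chart R".

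Under Assessment of clinical utility & statistical methods, the retests feed a Bland-Altman analysis that yields limits of agreement and a coefficient of repeatability, and these in turn are to supply a criterion of clinical significance. Under Study outcomes, reliability belongs to the primary outcome for current tests and to the secondary outcome for new tests. Under Study sample size, the data are meant to inform power and sample size in later trials.

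**The concern.** A test-retest coefficient is meant to describe how far two readings can differ when nothing has changed in the eye. If the second reading uses the letters of the first, two sources of disagreement are suppressed. Differences in difficulty between charts drop out, because the chart is the same. A participant who remembers letters or earlier guesses will also tend to repeat them. Both pull the two scores together. Recall of letters read correctly can also raise the second score.

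The rotation rule exists to prevent this, and the retest is where it matters most. The coefficient is to set a threshold for meaningful change. If it is too small, a later trial that relies on it could count ordinary measurement noise on the MAC as real change. If every MAC retest follows Table 2, no analysis of these data can separate recall from true repeatability.

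**Working it through.** **1. Chart used at each test and retest.** Table 2 contains three monocular test-retest pairs:

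| Test | Eye | First test | Retest | Chart changed? |
|---|---|---|---|---|
| Low luminance VA | Right | row 2, chart 1 | row 6, chart R | Yes |
| Standard VA | Right | row 3, chart 1 | row 7, chart R | Yes |
| MAC | Left | row 10, chart 2 | row 12, chart 2 | **No** |

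The MAC pair is the only one repeated on the same letters, with a single reading (row 11) in between.

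**2. Size under a simple model.** The document gives no standard deviation for MAC scores and no recall rate, so there is no stated figure to reproduce. Let each reading have error variance σ², and let ρ be the correlation between the two errors that the shared letters induce. Then

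Var(difference) = 2σ²(1 − ρ),

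and the width of the limits, relative to a retest on different letters (ρ = 0), is √(1 − ρ). For assumed values of ρ:

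- ρ = 0.1: √0.9 = 0.949, so the limits are 5% too narrow.
- ρ = 0.3: √0.7 = 0.837, so 16% too narrow.
- ρ = 0.5: √0.5 = 0.707, so 29% too narrow.

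**3. Direction under a letter-by-letter model.** A simulation used 14 rows of 5 letters, a 10% guess rate, letter difficulty with SD 0.05 logMAR and recall probability from 0 to 0.6. All of these inputs are assumptions. The coefficient of repeatability is 1.96 × SD of the differences, in letters. Drift means a real shift between the two readings, with SD 0.03 logMAR at each.

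| Retest | No drift | With drift |
|---|---|---|
| Different chart | 6.4 | 7.4 |
| Same chart, no recall | 6.2 | 7.2 |
| Same chart, recall 0.6, only correctly read letters recalled | 5.6 | 6.3 |
| Same chart, recall 0.6, all own responses recalled | 3.9 | 4.3 |

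Without drift, the narrowing is 1 − 6.17/6.38 = 3% with no recall, 1 − 5.62/6.38 = 12% when only correct letters are recalled, and 1 − 3.90/6.38 = 39% at the extreme. When only correct letters are recalled, the retest mean rises by about 0.5 letters at recall 0.1 and about 3 letters at recall 0.6. The same-chart coefficient was the smaller one in every scenario run.

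**4. Prior exposure in the ETDRS pairs.** Chart R is used at refraction (row 1) and again at the retests (rows 6 and 7). Chart 1 is not listed before row 2. For low luminance VA, the first test is therefore on letters not yet shown and the retest on letters used at refraction. For standard VA, each reading follows a low luminance reading on its own chart, and the retest has the refraction exposure in addition. This can shift the mean test-retest difference. The article does not say how much of chart R is read at refraction, so no size can be given.

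**The case against.** The strongest reply is that Table 2 does rotate. Consecutive MAC rows run 2, 1, 2, 1. If an assessment means one eye's block of testing, the ETDRS sequence also changes chart at each block: R, 1, 2, R, 1. On that reading the wording of the rule is kept, and the pairs of rows that share a chart (2-3, 4-5, 6-7 and 8-9) are no fault. This stands. The conflict is with the rule's purpose: alternating between eyes does not help when the retest returns the same eye to the same letters.

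A reader might also infer that the MAC would be declared more repeatable than the ETDRS tests because of the chart order. The document does not support that. It plans no ranking of tests by limits of agreement, and it judges appropriateness by spread, ceiling and floor effects, and separation of patients from controls. A direct comparison would in any case be blurred, because the MAC retest is on the left eye and the others on the right, and chart R had already been used at refraction.

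The size is also open to challenge, and rightly: nothing in the document points to one value of ρ. With little recall the narrowing is a few percent. Very uneven recall between participants could offset part of it. An upward shift in the retest mean would be visible as a Bland-Altman mean difference, so not all of the effect would be hidden. Finally, this is one retest pair for one test in an early-stage observational study. Row 12 does not affect the first MAC scores, the comparison of patients with controls, or the ETDRS retests.

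**Conclusion.** The point holds for the MAC repeatability pair. Rows 10 and 12 reuse chart 2 on the left eye, which defeats the purpose of rotation, and the resulting limits of agreement and coefficient of repeatability are likely too narrow. The direction is well supported by reasoning and by every simulated scenario, but it is an inference and not something the document states. The size is illustrative only: 5%, 16% or 29% for an assumed error correlation of 0.1, 0.3 or 0.5. The different exposure to chart R at VA and low luminance VA test and retest is a lesser point that bears on the mean difference. Table 2 should be changed because the remedy is cheap and the estimate serves a stated reliability outcome, but the flaw does not undermine the study as a whole.

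**What to change.** **MAC retest.** Run the left-eye retest in row 12 on a chart other than chart 2. If a third MAC chart exists, use it; Table 2 lists only charts 1 and 2 for the MAC. If not, retest the left eye on chart 1 directly after row 10, and then test the right eye. Relabelling row 12 as chart 1 without moving it would be weaker, because the participant would just have read chart 1 with the right eye.

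**Data already collected.** Report MAC repeatability from participants tested under the printed sequence separately, labelled as same-chart repeatability.

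**Chart R.** Where possible, refract on a chart that is not used for the VA and low luminance VA retests. With only charts R, 1 and 2 available, refracting on chart 2 would move the prior exposure to the left-eye readings in rows 4 and 5. If that is not acceptable, keep the sequence and note the unequal exposure when interpreting the mean test-retest difference.

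**Cost.** This is a worksheet edit with no added test time. The MAC limits may come out slightly wider. Under the two-chart fallback, the right eye reads MAC letters the participant has already seen, whichever chart is used, so its score carries a small memorisation risk that it does not carry now.
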